### 7.3 Semi-structured observation of the intervention

A semi-structured observation of the intervention will be conducted in week 1 and week 4 by a trained physiotherapist of the assessment team. The duration of the observation will be 50 min i.e., during the total RAGT duration and will not involve any additional effort of the study patient/participant. The structured part of the observation will involve the set-up and closure of the patient, the body position of the patient with relation to his or her trunk, lower and upper limbs, the reported percentage of the body weight support, the effort and potential fatigue or pain of the patient (that will be cared for as with any other rehabilitation strategy within a routine rehabilitation setting), the mimic and complexion/face colour of the patient, verbal and non-verbal utterings of the patient, verbal and non-verbal utterings of the therapist, the motivation of the patient, the communication between the patient and the therapist, the general atmosphere in the room, the overall environment and the overall

progression of the RAGT from week 1 to 4. In addition to the structured observation, an unstructured observation will be used to collect any other relevant information as to the performance of the patient and the conduct of the intervention.

#### **7.4 Concomitant treatment**

All study participants will receive their usual care including medical exams, rehabilitation assessments and goal setting, and medical treatment including medication. Study participants will undergo their usual inpatient rehabilitation comprising multidisciplinary rehabilitation (medical treatment, physiotherapy, occupational therapy, speech and language therapy, psychology counselling, dietetics etc.).

It is not planned to include patients who need relevant changes to their medication, but the medication will be adjusted and documented if the study PI considers this a requirement. Any changes or adjustments to medication that has an influence on the participant's walking ability/performance however will lead to the exclusion of the patient.

#### **7.5 Participant drop-out**

Study participants are free to withdraw their consent from the clinical investigation participation at any time without having to give a reason and without any consequences for their future treatment. In addition, patients may be withdrawn from the study by the PI if their health is in jeopardy.

The following points or events will lead to the patient's exclusion from the study if they occur after their initial admission in the study (dropout in terms of the biometric analysis):

- No questionnaire scores, assessment scores or LEXO® measures of interpretable quality.
- Withdrawal of consent to study participation by the study participant during integration into the study.
- An MS relapse or other disease exacerbation for any of the included diseases during the intervention period.
- Any changes or adjustments to medication that has an influence on the participant's walking ability/performance.

If the patient's health is jeopardised after the study intervention has started as a result of an unexpected deterioration in their state of health or general condition and/or mental/physical training is absolutely contraindicated, participation in the study will be ended immediately and a general physician or specialist will be consulted.

The reason for the patient's departure from the study will be documented in the CRF. The study is to be continued with the next identification number, with no replacement of study participants allowed. All patients leaving the study prematurely will be asked to undergo a

final examination with regard to their safety and as part of post-intervention testing at the next possible opportunity. The results of these tests will be documented in the CRF.

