### Recruitment, retention and adherence rates

The feasibility of the methods and of conducting a larger trial will be explored using predefined criteria, recording monthly recruitment and adherence rates to the RAGT intervention. Using a structured log, adherence to the RAGT will be recorded, including reasons (e.g., discontinuation due to lack of interest or injury). Any non-retention will also be recorded with reasons (e.g., consent withdrawn). ***This evaluation will not involve any***

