**Acceptability of the intervention**

Acceptability of the intervention will be assessed using a Smiley Likert Scale asking four predefined questions on the acceptance of the intervention (please see CRF), as well as a semi-structured observation during the RAGT intervention for understanding the intervention context and process, recognising patterns, and moving beyond selected outcome measures. This is of clinical relevance because high acceptability may help increase motivation and adherence in patients. ***The Likert scale will be used as part of the clinical investigation (2-4 min).***

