### **8.1. Handling of missing data**

The percentage of missing data will be recorded. Using Little's test of missing completely at random (MCAR) (Little, 1988) the type of missing data (MCAR, missing at random (MAR), missing not at random (MNAR)) will be checked, signified by a p-value >0.05.

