## **12.5 Data protection and confidentiality**

Personal data of the patients will be collected, forwarded, stored and evaluated as part of this clinical investigation only in accordance with the legal provisions of the General Data Protection Regulation (EU) 2016/679 (GDPR) and the Austrian Data Protection Act (DSG). This requires the voluntary consent of the patient in the informed consent form before participation in the clinical investigation. Patients will be informed of the following in the informed consent for this clinical trial:

1. Data collected as part of this clinical trial will be recorded on paper CRFs or electronic data carriers, treated strictly confidentially and forwarded without your name (pseudonymised) to
  - The principle investigator of the clinical investigation for the evaluation of adverse events,
  - The sponsor of the clinical investigation in the case of serious adverse events,
  - The statistician of the clinical investigation for scientific analysis,
  - The relevant ethics committee of the Medical University of Innsbruck to review that the clinical investigation is being conducted correctly as well as to evaluate clinical investigation results and adverse events.
2. Documents that contain personal data (e.g., the signed patient consent form, patient identification list) shall remain at the relevant clinical investigation site and is subject to investigators' confidentiality.
3. Insofar as this is necessary for reviewing the clinical study, authorised representatives of the relevant supervisory authorities bound to secrecy may inspect the personal data held by the investigator. The investigator shall be released from their duty of medical confidentiality for this purpose.

4. The consent to the collection and processing of personal data as part of this clinical study cannot be revoked. Patients will be informed that they can stop participation in the study at any time, without having to give a reason or without any subsequent disadvantages. In the event of withdrawal of consent, the data not containing my name stored up until this point may continue to be used, where this is required in order to determine the effects of the clinical investigation intervention and make sure that the legitimate interests of the person concerned are not impacted.

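### Section 7.5, read literally, takes leavers out of the adherence and acceptability results and must be reconciled with sections 4.8, 8.2 and 12.5

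*Protocol*

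**What the plan says.** Section 7.5 names four kinds of event that lead to "exclusion from the study if they occur after their initial admission in the study (dropout in terms of the biometric analysis". They are:

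- unusable data, in the section's own words: "No questionnaire scores, assessment scores or LEXO® measures of interpretable quality"
- the patient taking back consent
- a relapse in MS, or a worsening of any other included disease, while training is under way
- a medication change that affects walking.

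Leavers are not replaced. They are asked to attend a final examination as part of post-intervention testing, and its results go into the CRF. Section 9.5 refers to the same drop-out rule for patients whose training has to be stopped because of an incident.

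Section 4.8 makes feasibility the primary endpoint, assessed by recruitment, retention, adherence, adverse events, acceptability and observation. Its success criteria include 85% retention and 75% adherence (12 of 16 sessions). The adherence log is to record reasons such as "discontinuation due to lack of interest or injury", and non-retention is also logged with reasons. On acceptability it says: "Acceptability of the intervention will be assessed using a Smiley Likert Scale asking four predefined questions on the acceptance of the intervention".

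Section 8.2 (planned statistical analysis) defines retention as completers over the total sample, and adherence as sessions performed over sessions scheduled in the four weeks. The later section on missing data (numbered 8.1) says: "The percentage of missing data will be recorded". Under section 12.5, after withdrawal of consent, "the data not containing my name stored up until this point may continue to be used", subject to conditions.

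**The concern.** Two of the four triggers, withdrawal and unusable data, are among the things a feasibility study sets out to learn about. A patient who dislikes the training may well be the one who withdraws. If such patients leave the analysis together with their exclusion, adherence and acceptability describe only those who stayed, and the share of missing data is counted after the worst cases have gone.

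At stake is the 75% adherence criterion, one of three stated conditions for judging a full-scale randomised trial feasible. With 28 patients, three or four leavers carry real weight. In the four strata of two patients, one leaver is half the group.

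**Working it through.** **The passages side by side**

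| Place | What happens to a leaver |
|---|---|
| 7.5, list of events | Excluded; a dropout for the biometric analysis |
| 7.5, last paragraph | Asked for post-intervention testing, results recorded |
| 4.8 | Discontinuation logged under adherence; non-retention logged with reasons |
| 8.2 | Stays in the retention denominator; patient set for adherence not stated |
| 12.5 | Data stored before withdrawal may be used |

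The first row, taken literally, does not fit the other four.

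**Inputs from the protocol**

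- Sample size (5.3): 4 × 5 + 4 × 2 = 28, as stated.
- Adherence criterion (4.8): 12/16 = 75%, as stated.
- Sessions scheduled over all patients: 28 × 16 = 448. The criterion needs 0.75 × 448 = 336 performed.
- Expected attrition (5.3): 10% of 28 = 2.8, about 3 leavers.
- Retention criterion (4.8): 0.85 × 28 = 23.8, so 24 must complete. 24/28 = 85.7% passes and 23/28 = 82.1% fails. At most 4 can be lost.

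**Assumptions, not in the protocol**

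- Completers average 12.5 sessions.
- Each leaver attends between 2 and 8 sessions.
- Sessions are pooled, with 16 scheduled for every patient. The pooled rate then equals the mean of the individual rates.

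**Formula.** With d leavers, completer mean m and s sessions per leaver:

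- completers only: m/16
- all enrolled: [(28 − d) × m + d × s] / 448

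**Results**

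| Patients counted | s = 2 | s = 8 |
|---|---|---|
| Completers only | 12.5/16 = 78.1% | 78.1% |
| All 28, d = 3 | (312.5 + 6)/448 = 71.1% | (312.5 + 24)/448 = 75.1% |
| All 28, d = 4 | (300 + 8)/448 = 68.8% | (300 + 32)/448 = 74.1% |

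With 3 leavers the all-enrolled rate reaches 75% only if s is at least (336 − 312.5)/3 = 7.8. With 4 leavers, s must be at least (336 − 300)/4 = 9.

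**Range of completer adherence for which the choice decides the verdict.** All-enrolled adherence reaches 75% when completer adherence is at least (336 − d × s) / [(28 − d) × 16]. Here s is widened to 0 to 8.

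| | s = 0 | s = 4 | s = 8 |
|---|---|---|---|
| d = 3 | 336/400 = 84.0% | 324/400 = 81.0% | 312/400 = 78.0% |
| d = 4 | 336/384 = 87.5% | 320/384 = 83.3% | 304/384 = 79.2% |

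Completer adherence from 75% up to the figure in the cell passes among completers and fails over all enrolled. Above that figure both pass.

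**Retention.** The denominator is the total sample, so removing leavers from other analyses does not change it.

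**The case against.** The strongest reply is that section 7.5 nowhere says collected data are discarded. Its parenthesis can mean simply that the patient is counted as a dropout, and much of the protocol supports that reading. A withdrawal counts directly against the retention criterion. Section 5.2 has the physiotherapist log every session performed or not performed. The adherence formula is not restricted to completers, and leavers are invited to post-intervention testing. All of this stands, so removal from the feasibility results is one reading of the text rather than its plain statement.

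It can also be said that analysis sets belong in a statistical analysis plan, which is not at hand. That is fair as far as a missing definition goes. The point here is different: section 7.5 does state a rule, ties it to the analysis, and the rule sits badly with the protocol's other sections.

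A reader might infer more than the documents support:

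- *That the whole feasibility decision rests on survivors.* Retention does not, and the adherence set is not stated.
- *That acceptability could be pushed past a criterion.* It has no threshold and is summarised by median, range and quartiles. Even if 4 of 28 (14.3%) were unfavourable and all others favourable, the median and lower quartile would stay favourable.
- *That data completeness is a feasibility criterion.* Section 4.8 does not name it as one.
- *That the first bullet biases towards success.* It more naturally means that no usable data exist at all. If any single missing data type were enough, a patient with all sessions done could count as not retained, which would lower retention.

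Finally, the session counts are assumptions, and 12.5 lies just above the threshold of 12.

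**Conclusion.** The point holds as an inconsistency to be resolved. It does not establish that the primary endpoint is biased. Literally applied, section 7.5 takes leavers out of adherence and acceptability, against the drift of sections 4.8, 8.2 and 12.5.

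The demonstrable consequence is confined to the 75% adherence criterion. Under the stated assumptions, including leavers lowers adherence by 3.0 to 7.0 percentage points with 3 leavers (78.1% against 75.1% to 71.1%) and by 4.0 to 9.4 points with 4 (78.1% against 74.1% to 68.8%, unrounded 78.125 − 68.75 = 9.4). At the expected attrition the verdict may or may not change. With four leavers it changes across the whole assumed range. If completers attend nearly all sessions, the choice makes no difference to the verdict.

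**What to change.** 1. In sections 7.5 and 8.2, state that retention, adherence (16 scheduled sessions per patient), acceptability, adverse events and missing data are reported on all enrolled patients, using data up to withdrawal as section 12.5 permits. State that drop-out status under 7.5 affects at most the pre-post tests.
2. Replace the first bullet of 7.5, so that uninterpretable data make only the endpoint concerned missing for that patient.
3. Offer the four Likert questions at the final examination already requested of leavers. Report those who do not answer as a separate count, and do not score them as unfavourable.

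This concerns the analysis only; when a patient should stop training is left as it is. The cost is a few sentences of protocol text and a questionnaire that section 4.8 puts at 2 to 4 minutes. The downside is that adherence and acceptability may look slightly less favourable.

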|  | 
 
• Skin lesions in areas which get in contact with the device or the harness system (decubitus); infections, skin ulcers, late effects of previous injuries, especially of the lower extremity
 
• States of health preventing active rehabilitation (e.g., respiratory diseases, orthopaedic diseases, cognitive impairments restricting communication, aphasia, neuropsychological disorders, infections or inflammatory diseases, osteomyelitis)
 
• Severe apraxia
 
• Severe osteoarthritis in the area of the joints of the lower extremity
 
• Risk of autonomic dysreflexia (AD) in patients with spinal cord injury (SCI) with neurological levels of TH6 or cranial
 
• Reduced compliance
 
• Uncooperative or (self)aggressive behavior
 
• Cardiac diseases, e.g., heart failure and thoracotomy, uncontrolled orthostatic hypotension or other circulatory problems, circulatory disorders of the lower limbs
 
• Recent joint injury or endoprosthetics (e.g., total endoprosthetics, knee or hip joint replacement, reconstruction of the cruciate ligament or meniscus) with contraindicated ranges of movement or load limits
 
• Consolidated fractures in the area of the lower extremity within a period of 6 months after injury
 
• Insufficiently treated epilepsy
 
• Recently occurred seizures or increased risk of seizures
 
• Mechanical ventilation
 
• Lack of head control
 
• Long-term infusions (e.g., Baclofen pump, intrathecal pumps, PEG tube ...) or
 
• stimulators (e.g., pacemakers, nerve stimulators)
 
• Enterostomy/ostomy
 
• Sensory impairments of the lower extremities and the torso, especially reduced sensation of pain
 
• Pregnancy as assessed by a pregnancy test in women of childbearing age before enrolment into the study
 
• An MS relapse or other disease exacerbation for any of the included diseases during the intervention period will lead to the exclusion of a participant from the study
 
 |

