The first phase of the analysis will involve a descriptive analysis for all disease groups using the mean (SD) or median (range, 25th and 75th percentiles). The second phase of the analysis will include inferential statistics using a pre-post analysis of the data from the total sample (one group). For continuous data, a paired t-test will be performed and for ordinal data, a Wilcoxon Signed Rank test.

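### Relapses and exacerbations after enrolment count as drop-outs for the analysis, which conflicts with the total-sample pre-post test and would shift it toward benefit; the Little's-test statement is also wrong

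*Protocol*

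**What the plan says.** Protocol section 7.5 opens its list with "The following points or events will lead to the patient's exclusion from the study if they occur after their initial admission in the study" and calls such a case a "dropout in terms of the biometric analysis". The list has four items: no data of interpretable quality, withdrawal of consent, "An MS relapse or other disease exacerbation for any of the included diseases during the intervention period", and "Any changes or adjustments to medication that has an influence on the participant's walking ability/performance". The synopsis repeats the relapse rule among the exclusion criteria ("during the intervention period will lead to the exclusion of a participant from the study"). The medication rule recurs in the synopsis and in sections 5.5 and 7.4. Leavers are not replaced.

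Section 7.5 also states: "All patients leaving the study prematurely will be asked to undergo a" final examination. This serves safety and post-intervention testing, and its results go into the CRF.

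The planned statistical analysis (8.2) compares before with after "using a pre-post analysis of the data from the total sample (one group"), by paired t-test or Wilcoxon signed rank test at two-sided 0.05. The section on handling missing data, numbered 8.1 for a second time, says that with Little's test "the type of missing data (MCAR, missing at random (MAR), missing not at random (MNAR)) will be checked, signified by a p-value" above 0.05.

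**The concern.** A relapse or exacerbation is a worsening of the disease whose walking, balance and fatigue outcomes are being tested. If such patients leave the analysis because of that event, the patients who remain are selected partly on outcome. The limitations section states that there is no control group, so no comparison arm undergoes the same selection and the shift goes straight into the estimated change.

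The overall pre-post test is the only efficacy test the protocol allows itself; the limitations section rules out testing by disease group. Its result feeds the report on preliminary effectiveness to the sponsor (7.8) and the hypotheses of the follow-up randomised trial (4.1).

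The protocol does not settle the matter. Section 7.5 puts these patients outside the analysis, 8.2 refers to the total sample, and the final examination supplies a value that could be used.

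**Working it through.** **Inputs from the protocol.** N = 4×5 + 4×2 = 28, which agrees with section 5.3. Expected attrition is 10% (5.3): 0.10×28 = 2.8, about 3 patients. The retention target is 85% (4.8): 0.85×28 = 23.8, so at least 24 must stay and at most 4 may be lost.

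**Assumptions, because the protocol gives no SD, effect size or exacerbation rate.** Change scores are independent N(0,1) with a true mean of 0, and positive means improvement. Outcome-related losses are the k patients lowest on a score that has correlation ρ with change. Any other losses are random. A two-sided 5% paired t-test is run on the remaining patients. False benefit is a significant result in the favourable direction, nominally 2.5%.

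**Mean shift by formula.** Shift = ρ × (sum of the absolute expected values of the k lowest of 28 standard normals) / (28 − k). Random further losses do not change it. The three lowest have expected values −2.014, −1.581 and −1.327.
- k = 1, ρ = 0.5: 0.5×2.014/27 = 0.037
- k = 1, ρ = 1: 2.014/27 = 0.075
- k = 3, ρ = 1: (2.014 + 1.581 + 1.327)/25 = 4.922/25 = 0.197

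**Simulation, 60,000 trials per row.**

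| Losses among 28 | Mean shift (SD) | False benefit |
|---|---|---|
| None | 0.00 | 2.5% |
| 3, unrelated to change | 0.00 | 2.5% |
| 1 outcome-related (ρ = 0.5) + 2 random | +0.04 | about 4% |
| 1 outcome-related (ρ = 1) + 2 random | +0.07 | about 6.5% |
| 3 at ρ = 0.3 | +0.06 | 4.9% |
| 3 at ρ = 0.5 | +0.10 | 7.7% |
| 3 at ρ = 0.8 | +0.16 | 14.5% |
| 3 worst changers (ρ = 1) | +0.20 | 22.5% |
| 4 worst changers (the most the 85% target allows) | +0.25 | 32.8% |

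**Reverse case.** If the excluded patients had improved, for example after a drug adjustment that helped walking, removing the best 1, 2 or 3 shifts the mean by −0.07, −0.14 or −0.20 SD.

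**Little's test.** The null hypothesis is MCAR. The test compares observed means between missingness patterns. If all baselines are present and only T2 is missing, it compares the baselines of patients with and without T2. MAR and MNAR differ in how missingness depends on unobserved values, so no test on the observed data can separate them. Rejection would argue against MCAR without saying which alternative holds. Non-rejection with about 3 incomplete cases shows very little. When missingness was made to depend only on change, p exceeded 0.05 in 94.8% of 20,000 simulated trials. That follows from the construction, but it shows that the test cannot see this kind of loss.

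**The case against.** The best defence is that the protocol may not discard anyone. It names the total sample as the analysis population and collects the final examination as post-intervention testing. A reader might infer from the drop-out label that these values are thrown away, but no section says so. What stands is a conflict that has to be resolved.

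Further limits also stand:
- A reader might infer that every patient withdrawn for deteriorating health is removed from the analysis. The label covers only the four listed items. Jeopardised health and unexpected deterioration are in separate sentences, and section 9.5 refers serious events to 7.5 without the analysis label.
- A reader might infer that the medication rule also favours the device. It covers changes in either direction, and it can be read as removing a co-intervention in an uncontrolled design.
- The 10% attrition is general, two of the four listed items need not relate to outcome, patients must be clinically stable at entry, and the intervention lasts four weeks. Three outcome-driven losses of exactly the worst changers is an extreme case.
- The feasibility endpoint is not distorted. Retention is divided by the total sample, and non-retention is recorded with reasons.
- Little's test is presented as a general check on missing data, not as a safeguard for these exclusions. Section 8.2 and the synopsis describe it as a check of MCAR only; the wider claim is in the missing-data section.

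None of this removes the core. An analysis drop-out label tied to relapse is written into the protocol, so a statistical analysis plan that kept these patients would contradict it.

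**Conclusion.** The point holds in this form. Sections 7.5 and 8.2 disagree on who enters the pre-post analysis. If 7.5 governs, excluding relapses and exacerbations biases the secondary pre-post changes toward benefit; for medication changes the sign is not fixed.

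At about the expected attrition, with no true change and n = 28, the plausible range is from +0.04 SD and 4% false benefit to an upper bound of +0.20 SD and 22%, against 2.5%. The upper figure is a bound and should not be read as the expected error. The range rests on normal change scores, a t-test and assumed correlations. Many motor endpoints apply only to ambulatory or only to non-ambulatory patients, so their n is below 28; the Wilcoxon test was not simulated.

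A reader might infer that the follow-up trial will be sized on an inflated effect. The protocol says only that this study will inform its hypotheses and design.

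The claim that Little's test reveals the type of missing data is wrong whichever analysis set is chosen.

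**What to change.** Leave the clinical withdrawal rules as they are and change only the analysis wording.

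1. In 7.5, delete the analysis drop-out label for the relapse/exacerbation and medication-change events.
2. In 8.2, state that every enrolled patient with a baseline and any post-intervention or final examination enters the pre-post analysis with the event flagged. Report the analysis without the flagged patients as a sensitivity analysis.
3. In the missing-data section, replace the claim about Little's test with a table of missingness by reason.

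The cost is wording only, since the final examination is already planned. The downsides are that T2 falls at different times for early leavers, and that some final examinations will not be obtained because patients are only asked to attend. Those patients still cannot contribute a pair and should appear in the table of reasons.
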